#### 9.3.2 Monitoring pregnancies for potential Serious Adverse Events

The trial will exclude patients younger 50 years to avoid cases of pregnancies of the female participants. In the event that a male participant's partner becomes pregnant, there is no identified risk of congenital anomalies or birth defects in the offspring. There will therefore be no monitoring of pregnancies outcome.

### 9.4 Reporting period

Details of all AEs will be documented and reported from the date of consent (screening) until 7 days after the last dose.

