### 3. TRIAL DESIGN

#### 3.1 Trial Design

This is a double-blind, 2 year randomised, placebo-controlled single centre trial, recruiting 250 participants from primary and secondary care. Eligible participants will present with symptoms of permanent AF levels and will be randomised to receive a 2 year treatment with either Spironolactone or placebo.

Prior to screening and recruitment of participants, the trial protocol will be finalised, practices recruited, research staff trained, initial eligibility screening in general practices undertaken to identify potential participants (Figure 3). Trial committees will meet to plan their respective committee charters and operating procedures.

Preliminary eligibility for the trial will be checked by the participants' GPs prior to patients being invited for the screening visit to the RC-CCS. Potential participants will be invited to attend an appointment at the trial site for an initial screening visit. They will be asked to bring their medication with them to the visit. At the screening visit, participants will be consented into the study and screened for eligibility. Eligible participants will be given the option of having the baseline visit straight after the screening visit or on a separate date. During the baseline visit, they will be randomised into the trial, subject to meeting the inclusion and exclusion criteria. Baseline parameters will be recorded. Participants will be randomised to receive a 2 year treatment with either Spironolactone or placebo and will be required to attend follow-up visits during the 2 year treatment period. The end of the trial will be defined as the date of the last visit of the last participant undergoing the trial.

After the recruitment the participants will have follow-up visits at 1, 3, 6, 9, 12, 15, 18, 21 months for assessment of clinical status, measurement of blood pressure, potassium, sodium, full blood count/hematocrit and renal function. Trial medication will be dispensed at baseline, 6 months, 12 months and 18 months. Quality of life will be assessed at baseline, 12 months and 24 months using the EQ-5D and the MLWHF questionnaires.

The final visit will be done at 24 months from the randomisation to assess the primary and secondary outcomes. The statistical analysis will be completed in year 4 of the trial (months 40-42).

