### 7.2 Treatment and Dosing Schedule

Trial participants will receive either Spironolactone or matched placebo according to the following instructions:

- a single 25 milligram tablet
- to be taken orally once per day (typically to be taken during the morning, but can be taken regularly at other time of day if preferable).
- to be taken with a drink to help swallowing of the drug
- for a 24 month period

In the case of an increase in potassium level to 5.1-5.5 mmol/L or in the presence of other non-life-threatening side effects (such as gynaecomastia), the trial drug will be down-titrated to 25 mg each second day. In such cases, the investigators are advised to re-up-titrate the trial medication if the reason for down-titration has resolved. Routine laboratory surveillance of serum potassium, sodium, full blood count with hematocrit, and renal function will be done by protocol at each visit and within 1 week of any dose adjustment.

Drug toxicity will be defined as an increase in potassium level to >5.5 mmol/L. In the case of toxicity or suspected toxicity, the trial medication will be stopped for the duration of the trial, but the patient will be requested to attend the remaining follow up visits.

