#### Final Visit (24 months from randomisation)

- Standard clinical examination (including BP measurement),
  - Medication review
  - Repeat ECG
  - Repeat echocardiogram
  - Repeat Brain Natriuretic Peptide (BNP) level test using point of care device
  - Repeat Cardiopulmonary exercise testing (CPET) with determination of peak VO2
  - Repeat 6-minute walk test
  - Blood sample taken: potassium, sodium, full blood count (including hematocrit) and renal function
  - EQ-5D and MLWHF quality of life questionnaires will be completed
- If the patient has an indication for spironolactone, the participants GP will be informed. No further follow up will be arranged. The GP will be informed about the trial completion.

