## 9. ADVERSE EVENT REPORTING

### 9.1 Reporting Requirements

The collection and reporting of Adverse Events (AEs) will be in accordance with the Medicines for Human Use Clinical Trials Regulations 2004 and its subsequent amendments. The CI or PI will assess the seriousness and causality of all AEs experienced by the participant, and the CI will assess the expectedness of all SARs. This will be documented in the source data with reference to the safety information contained within the Summary of Medicinal Product Characteristics (SmPC).

Spironolactone has a half-life of about 1–2 hours, but it has active metabolites with longer half-lives. Therefore the end point for the reporting of serious adverse event will be 7 days after the last dose.

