### 9.2 Adverse Events (AE)

All medical occurrences which meet the definition of an AE should be recorded on the AE pages of the CRF. Please note this includes abnormal laboratory findings. All AEs recorded on the AE CRF must be followed up to resolution and patients must be asked if they have experienced any AEs at every visit.

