## 9.9 Data Monitoring and Ethics Committee

Data analyses will be supplied in confidence to an independent Data Monitoring and Ethics Committee (DMEC), which will be asked to give advice on whether the accumulated data from the trial, together with the results from other relevant research, justifies the continuing recruitment of further participants. The DMC will operate in accordance with a trial specific charter based upon the template created by the Damocles Group. The DMC will meet every 6 months unless there is a specific reason (e.g. safety phase) to amend the schedule. The DMEC will review all SAEs.

|                          |            |               |            |       |          |
|--------------------------|------------|---------------|------------|-------|----------|
| Trial name:              | IMPRESS-AF |               |            |       |          |
| Protocol version number: | 6.0        | version date: | 12/10/2015 | Page: | 37 of 67 |

Additional meetings may be called if recruitment is much faster than anticipated and the DMC may, at their discretion, request to meet more frequently or continue to meet following completion of recruitment. An emergency meeting may also be convened if a safety issue is identified. The DMC will report directly to the Trial Steering Committee who will convey the findings of the DMC to the sponsor. The DMEC may consider recommending the discontinuation of the trial if the recruitment rate or data quality are unacceptable or if any issues are identified which may compromise participant safety. The trial would also stop early if the interim analyses showed differences between treatments that were deemed to be convincing to the clinical community.

The trial may be stopped due to poor recruitment.

The DMEC will be responsible for the regular monitoring of trial data. The DMEC will assess the progress of the trial and give advice on whether the accumulated data from the trial, together with the results from other relevant trials, justifies the continuing recruitment of further participants. The committee will meet in person or by teleconference prior to the trial commencing and then three and six months after initiation of the trial. The DMC will make confidential recommendations to the TSC as the decision –making committee for the trial.

Currently agreed DMEC members

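### AE and SAE reporting closes 7 days after each participant's last dose, so new SAEs after early stopping leave formal safety reporting although the trial follows participants for 24 months

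*Protocol*

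**What the plan says.** - **Reporting window.** Section 9.4: "Details of all AEs will be documented and reported from the date of consent (screening) until 7 days after the last dose". Section 9.1 argues from the half-life of the drug and its metabolites that "the end point for the reporting of serious adverse event will be 7 days after the last dose".
- **Follow-up.** Section 3.1: "The final visit will be done at 24 months from the randomisation to assess the primary and secondary outcomes". Section 8.4 withdraws a participant from the trial itself only when consent is revoked.
- **After a stop for toxicity (potassium above 5.5 mmol/L).** Section 7.2: "the patient will be requested to attend the remaining follow up visits".
- **After withdrawal from trial medication generally, with the same potassium trigger listed.** Section 8.4 names only quality-of-life questionnaires at months 12 and 24. Section 8.3 (Additional Visits) does the same for voluntary withdrawal from treatment, and section 6.3 after a code break.
- **AE enquiry.** Section 9.2: "patients must be asked if they have experienced any AEs at every visit".
- **Oversight.** Section 9.9: "The DMEC will review all SAEs".
- **Outcomes outside the SAE form.** All-cause hospitalisation over two years is a secondary outcome (Trial Summary and section 2.2). The Trial Summary also records death from any cause and other major clinical events. Section 8.3 collects hospitalisations, MACE and safety outcomes at the month 1 to 21 visits.

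**The concern.** A window tied to the last dose suits an on-treatment display of drug toxicity. It fits poorly with a trial that keeps participants for 24 months and analyses by intention to treat (section 13.1). Section 9.2 asks about AEs at visits where section 9.4 no longer has them documented.

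The truncation may also differ by arm. Section 8.4 lists high potassium, renal impairment and breast symptoms as reasons to stop, and section 8.3 expects potassium rises from spironolactone. If more participants stop on active drug, that arm has less time in which an SAE can be reported.

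The SAE form feeds SUSAR classification (sections 9.5.2 and 9.6), regulatory reporting (9.7) and the DMEC's SAE review (9.9). An SAE that was never reported cannot be restored to those streams by a later analysis.

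**Working it through.** **1. Length of the gap.** Seven days is 7/30.44 = 0.23 months. A participant who stops at month m has 24 − m − 0.23 months of planned follow-up outside the window. For a stop at month 3 this is 24 − 3 − 0.23 = 20.8 months.

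**2. What happens to each kind of event in that gap.**
- *New SAE of any kind, including death or admission:* closed to SAE reporting by 9.1 and 9.4, and so absent from the SAEs that the DMEC reviews.
- *Death, hospitalisation, MACE as outcomes:* still collected under the Trial Summary, 2.2 and 8.3, none of which ties collection to dosing. This works only if the participant is seen. Section 7.2 implies full visits; 6.3, 8.3 (Additional Visits) and 8.4 name only questionnaires.
- *Any other new AE:* 9.2 says ask, 9.4 says the period is over. It may not be recorded.
- *An event already recorded before the window closed:* followed to resolution or stabilisation (9.2, 9.5.3, 9.6.1). Not lost.

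**3. Illustration of the effect on SAE counts.** Inputs:
- Sample size from 13.1.1: 200/0.8 = 250, which reproduces the stated total. One-to-one allocation gives 125 per arm.
- Event rate from 13.1.1: about 20% admissions a year, read here as 0.20 per person-year, equal in both arms and unchanged by stopping. Admissions stand in for SAEs because hospitalisation meets the SAE definition in section 20.
- Stopping proportions and times: assumptions. The protocol gives none by arm.

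Expected events per arm: 125 × 2 × 0.20 = 50.

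Share of follow-up lost per stopper: L = (24 − m − 0.23)/24. This gives L = 0.949 at month 1, 0.740 at month 6 and 0.490 at month 12. With stopping spread evenly over 24 months, L = (24 − 0.23)²/(2 × 24²) = 0.490.

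Events reaching SAE forms: 50 × (1 − pL), where p is the proportion stopping. The ratio is (1 − p_spiro L)/(1 − p_plac L). The event rate cancels, so the ratio depends only on stopping.

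| Stopping, spironolactone vs placebo | Timing | Counted, spironolactone | Counted, placebo | Ratio |
|---|---|---|---|---|
| 10% vs 5% | month 12 | 47.5 | 48.8 | 0.975 |
| 15% vs 5% | month 6 | 44.4 | 48.1 | 0.923 |
| 20% vs 10% | month 6 | 42.6 | 46.3 | 0.920 |
| 20% vs 10% | even | 45.1 | 47.5 | 0.948 |
| 20% vs 10% | month 1 | 40.5 | 45.3 | 0.895 |
| 30% vs 10% | even | 42.6 | 47.5 | 0.897 |
| 30% vs 10% | month 1 | 35.8 | 45.3 | 0.790 |

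Worked row, 15% vs 5%: lost events are 50 × 0.15 × 0.740 = 5.6 and 50 × 0.05 × 0.740 = 1.9, so the ratio is 44.4/48.1 = 0.923. With equal stopping at equal times the ratio is 1.00. The true ratio is 1.00 in every row.

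**The case against.** A reader might infer that deaths and hospital admissions go uncounted for the rest of the two years. The documents do not support that. Sections 2.2 and 8.3 and the Trial Summary collect them as outcomes whatever the dosing, so the ratios above describe SAE-form counts only and not the secondary hospitalisation outcome.

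Other points on that side:
- **No between-arm SAE comparison is specified.** The protocol states no safety set or denominator; these may sit in the SAP. The count bias arises only if SAEs are compared per randomised participant. A rate per on-treatment person-time would not show it in that form, though it would still omit later events. This stands, and it makes the bias conditional.
- **The DMEC also receives data analyses (9.9).** It may see deaths and admissions that way, so it is not blind to the later course of participants who stopped. This stands. But outcome data do not replace causality assessment, SUSAR classification or 24-hour reporting.
- **SAE forms were never a complete safety source.** Section 9.3.1 sends hyperkalaemia, creatinine rises and side effects requiring withdrawal to routine CRFs. True, but new SAEs outside that list still depend on the form.
- **The window is explicit, consistent between 9.1 and 9.4, and reasoned from half-life.** True, but the half-life argument addresses attribution to the drug, not the comparison of randomised arms.

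For completers, the 7-day tail falls after the final visit, and section 8.3 says "No further follow up will be arranged". This is a small mismatch that affects both arms alike. Section 9.5.2 triggers reporting when staff become aware of an event, so no extra contact is needed.

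**Conclusion.** The point holds in this form: after early stopping, new SAEs leave formal SAE reporting and the DMEC's SAE review, and new AEs other than hospitalisations and MACE may go unrecorded. Deaths, hospitalisations and MACE remain outcomes, with uncertain capture because section 7.2 and section 8.4 do not match for the same potassium trigger.

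A bias in SAE counts towards the arm with more stopping is plausible in direction and unknown in size. The illustrative ratios are about 0.92 to 0.975 under moderate assumed stopping, and 0.79 if 30% vs 10% stop at month 1. They rest on assumed stopping, equal and constant event rates, and a comparison per randomised participant. This is an inexpensive improvement worth making while data are still being collected. It does not show that the efficacy outcomes are biased.

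**What to change.** 1. In 9.1 and 9.4, run SAE reporting (including death and hospitalisation) from consent to the month-24 visit or 7 days after the last dose, whichever is later, whether or not trial medication has stopped.
2. Show SAEs to the DMEC by randomised arm for that full period, with on-treatment plus 7 days as a secondary display.
3. Reconcile 6.3, 7.2, 8.3, 8.4, 9.1, 9.2 and 9.4 so that they agree on which visits and data are collected after trial medication stops, including whether new non-serious AEs are recorded.

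Cost: an amendment to a few sentences and a few more SAE forms for participants off drug, mostly at visits already scheduled.

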### 9.5 Reporting Procedure – At Site

#### 9.5.1 Adverse Events

AEs should be collected on an AE Form (and where applicable on an SAE Form). An AE Form should be completed at each visit where applicable.

|                          |            |               |            |       |          |
|--------------------------|------------|---------------|------------|-------|----------|
| Trial name:              | IMPRESS-AF |               |            |       |          |
| Protocol version number: | 6.0        | version date: | 12/10/2015 | Page: | 35 of 67 |

### 9.5.2 Serious Adverse Events

AEs defined as serious and which require reporting as an SAE should be reported on an SAE Form. When completing the form, the Investigator will be asked to define the causality and severity. The CI will also assess all SARs for expectedness. If the event meets the definition of a SAR that is unexpected (i.e. is not defined in the Reference Safety Information (RSI) it will be classified as a Suspected Unexpected Serious Adverse Reaction (SUSAR).

On becoming aware that a participant has experienced an SAE, the Investigator (or delegate) must complete, date and sign an SAE Form. The form should be faxed to the PC-CRTU trials team using one of the numbers listed below as soon as possible and no later than 24 hours after first becoming aware of the event:

**To report an SAE, fax the SAE Form to: [name]**

On receipt the PC-CRTU trials team will allocate each SAE a unique reference number which will be forwarded to the site as proof of receipt. If confirmation of receipt is not received within 1 working day please contact the PC-CRTU trials team. The SAE reference number should be quoted on all correspondence and follow-up reports regarding the SAE and filed with the actual SAE in the Site File.

For SAE Forms completed by someone other than the Investigator the Investigator will be required to countersign the original SAE Form to confirm agreement with the causality and severity assessments. The form should then be returned to the PC-CRTU trials team and a copy kept in the Site File.

Investigators should also report SAEs to their own Trust in accordance with local practice.

### 9.5.3 Provision of follow-up information

Participants should be followed up until resolution or stabilisation of the event. Follow-up information should ideally be provided on a new SAE Form.

## 9.6 Reporting Procedure – PC-CRTU

On receipt the PC-CRTU trials team will allocate each SAE a unique reference number which will be forwarded to the site as proof of receipt within 1 working day. The SAE reference number will be quoted on all correspondence and follow-up reports regarding the SAE and filed with the actual SAE in the TMF. If the event meets the definition of a SAR that is unexpected (i.e. is not defined in the Reference Safety Information (RSI) it will be classified as a Suspected Unexpected Serious Adverse Reaction (SUSAR).

### 9.6.1 Provision of follow-up information

Participants should be followed up until resolution or stabilisation of the event. Follow-up information should ideally be provided on a new SAE Form.

## 9.7 Reporting to the Competent Authority and main Research Ethics Committee

### 9.7.1 Suspected Unexpected Serious Adverse Reactions

PC-CRTU will report a minimal data set of all individual events categorised as a fatal or life threatening SUSAR to the Medicines and Healthcare products Regulatory Agency (MHRA), main Research Ethics Committee (REC) and RGT within 7 days. Detailed follow-up information will be provided within an additional 8 days.

All other events categorised as SUSARs will be reported within 15 days.

|                          |            |               |            |       |          |
|--------------------------|------------|---------------|------------|-------|----------|
| Trial name:              | IMPRESS-AF |               |            |       |          |
| Protocol version number: | 6.0        | version date: | 12/10/2015 | Page: | 36 of 67 |

### 9.7.2 Serious Adverse Reactions

PC-CRTU will report details of all SAEs and SARs (including SUSARs) to the MHRA, main REC and RGT annually from the date of the Clinical Trial Authorisation, in the form of a Development Safety Update Report (DSUR).

### 9.7.3 Adverse Events

Details of all AEs will be reported to the MHRA on request.

### 9.7.4 Other safety issues identified during the course of the trial

The MHRA, main REC and RGT will be notified immediately if a significant safety issue is identified during the course of the trial.

Details of all SUSARs and any other safety issue which arises during the course of the trial will be reported to Principal Investigators. A copy of any such correspondence should be filed in the Site File.

## 9.9 Data Monitoring and Ethics Committee

Data analyses will be supplied in confidence to an independent Data Monitoring and Ethics Committee (DMEC), which will be asked to give advice on whether the accumulated data from the trial, together with the results from other relevant research, justifies the continuing recruitment of further participants. The DMC will operate in accordance with a trial specific charter based upon the template created by the Damocles Group. The DMC will meet every 6 months unless there is a specific reason (e.g. safety phase) to amend the schedule. The DMEC will review all SAEs.

|                          |            |               |            |       |          |
|--------------------------|------------|---------------|------------|-------|----------|
| Trial name:              | IMPRESS-AF |               |            |       |          |
| Protocol version number: | 6.0        | version date: | 12/10/2015 | Page: | 37 of 67 |

Additional meetings may be called if recruitment is much faster than anticipated and the DMC may, at their discretion, request to meet more frequently or continue to meet following completion of recruitment. An emergency meeting may also be convened if a safety issue is identified. The DMC will report directly to the Trial Steering Committee who will convey the findings of the DMC to the sponsor. The DMEC may consider recommending the discontinuation of the trial if the recruitment rate or data quality are unacceptable or if any issues are identified which may compromise participant safety. The trial would also stop early if the interim analyses showed differences between treatments that were deemed to be convincing to the clinical community.

The trial may be stopped due to poor recruitment.

The DMEC will be responsible for the regular monitoring of trial data. The DMEC will assess the progress of the trial and give advice on whether the accumulated data from the trial, together with the results from other relevant trials, justifies the continuing recruitment of further participants. The committee will meet in person or by teleconference prior to the trial commencing and then three and six months after initiation of the trial. The DMC will make confidential recommendations to the TSC as the decision –making committee for the trial.

Currently agreed DMEC members

